## Aim of this study

The primary aim of this study is to determine the effect of probiotic organisms, ingested daily by VLBW preterm infants (below 1500 g and less than 32 weeks' gestation at birth) from shortly after birth, on the incidence of definite late onset sepsis, diagnosed after 48 hours of age and before term or discharge home, whichever occurs sooner. A secondary aim is to investigate the effects of probiotics on allergic diseases in this population.

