## Background

### The intestinal microbial community and probiotics

Late onset sepsis (> 48 hours after birth) is a frequent complication in very preterm infants with high mortality and morbidity. In 2003, the Australian and New Zealand Neonatal Network (ANZNN) reported an incidence of 23% in very low birth weight infants (VLBW, less than 1500 grams) and 31% in extremely low birth weight infants (ELBW, less than1000 grams), with 18% mortality [1]. Preterm infants are more susceptible to infection as they have an immature immune system, which may in part be due to the abnormal development of their gastrointestinal microflora (microbiome). Molecular microbiological studies estimate that the mature human intestinal microbiome encompasses several hundred species of microorganisms with concentrations approximating 10^12 ^viable microbes per gram of faecal content [2]. This microbiome performs numerous important functions, including the digestion of macro and micronutrients, regulation of host fat storage, the metabolism of endogenous and exogenous compounds, immunoregulation and limiting colonisation with pathogenic microbes [3,4]. Disturbance of the gastrointestinal tract microbial environment may predispose individuals to a variety of diseases ranging from inflammatory bowel disease to allergy and obesity [4-7].

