#### • Study population

##### Inclusion criteria

a. Preterm infants both below 1500 g and less than 32 weeks' gestational age at birth

b. Enrolled within 72 hours of birth

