##### Exclusion criteria

a. Major or suspected major congenital anomalies

b. Considered likely to die within 72 hours of birth

c. Parents from whom informed consent cannot be obtained. Babies of mothers who are already taking supplemental probiotics by capsule (not yoghurt, etc.)

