### Outcomes

• **The primary outcome is the incidence of at least one episode of definite (blood culture positive) late onset sepsis before 40 weeks corrected age or discharge home, whichever occurs sooner.**

• The secondary outcomes are:

- incidence of clinically-suspected sepsis (blood culture negative sepsis)

- NEC, graded by modified Bell's criteria [37]

- mortality

- duration of the primary hospital admission

- number of courses of antibiotics

- number of days until full enteral feeds established (120 ml/kg/day or more for 3 consecutive days)

- In a subgroup of Victorian subjects at 12 months' corrected age:

(i) growth, including weight, length and head circumference

(ii) infections, hospital admissions and antibiotic courses

(iii) cumulative incidence of allergic disease, including atopic eczema, food allergy, and asthma/wheeze at 12 months as assessed by questionnaire [69,70]

(iv) immunological parameters including serum immunoglobulins, number of T- regulatory cells (Tregs) and levels of T- regulatory cytokines (Interleukin-10 and Transforming Growth Factor-β (TGFβ)) produced by mononuclear cells in-vitro [70].

(v) allergic sensitisation at 12 months - skin prick testing to a panel of common allergens (Egg white, milk, peanut, cat hair, grass pollen and house dust mite)

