#### • Statistical Analysis

Intention to treat analysis: Data from all randomised participants will be considered in the intention-to-treat model (for the primary outcome).

Per protocol analysis: Per protocol evaluation will exclude data from participants who did not receive the intervention.

Interim analyses: An independent data monitoring committee (DMC) consisting of an independent paediatrician with expertise in neonatal sepsis, an epidemiologist, and two neonatologists with clinical trials experience has been appointed. Full interim analyses of all outcomes are being undertaken as data is received when 100, 400 and 700 recruits have completed the study. An additional interim analysis of mortality occurred when 200 participants reached term corrected age. Any adverse events, which on further assessment appear likely to be due to the probiotics, are reported to the clinical trial steering committee, the local hospital research committees at participating centres and where appropriate, the Therapeutic Goods Administration.

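### Sepsis is counted from 48 hours of age but enrolment runs to 72 hours, so a few events before randomisation may count and slightly dilute the effect

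*Protocol article*

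**What the plan says.** The start of the outcome is tied to age. The Aim of this study section counts "definite late onset sepsis, diagnosed after 48 hours of age and before term or discharge home, whichever occurs sooner", and the Background uses the same 48-hour threshold from birth to define late onset sepsis.

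The Outcomes section gives the primary outcome as "at least one episode of definite (blood culture positive) late onset sepsis before 40 weeks corrected age or discharge home", whichever is sooner. That fixes the end of the window but does not place its start at randomisation.

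The inclusion criteria ask that infants be "Enrolled within 72 hours of birth". The exclusion criteria cover anomalies, infants "Considered likely to die within 72 hours of birth", absence of consent, and mothers taking probiotic capsules. None concerns sepsis or a positive blood culture before entry. The Statistical Analysis section puts all randomised infants into the intention-to-treat analysis of the primary outcome.

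**The concern.** The two clocks overlap by up to 24 hours. An infant with a positive culture at 50 hours who is randomised at 70 hours meets the primary outcome before allocation, and nothing in the article removes that event.

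This has two consequences. Allocation cannot change the event, so it adds equally to both arms in expectation and pulls the risk ratio towards 1. And because the outcome is at least one episode, that infant is already a case, so preventing a later episode no longer shows. What is at stake is some dilution and some power in a trial planned close to 80%.

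**Working it through.** **Inputs from the article.** Control risk 23%, target risk 16%, power 0.8, two-sided alpha 0.05, 530 per group, 1,100 recruited (Sample size calculation). Allocation is equal within blocks (Randomisation), so 550 per group. The outcome starts at 48 h of age (Aim), enrolment closes at 72 h (Inclusion criteria) and the outcome ends at 40 weeks or discharge (Outcomes).

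**Assumptions, because the article gives no figure.** Events fall evenly over about 56 days (32 to 40 weeks). Two enrolment patterns are used: uniform over 0–72 h, and everyone at 72 h. Randomisation is taken to coincide with enrolment.

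**Step 1: reproduce the plan.** With d = 0.07 and mean risk 0.195:

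n0 = [1.960 × √(2 × 0.195 × 0.805) + 0.842 × √(0.23 × 0.77 + 0.16 × 0.84)]² / 0.07² = 501.7

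n = (n0/4) × [1 + √(1 + 4/(n0 × d))]² = 529.9, so 530.

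The planned figure is reproduced exactly with the continuity correction (502 without it). Solving the same formula for power at 550 per group gives 81.5%, which is the reference below.

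**Step 2: share of events before randomisation (q).** The even rate is 23/56 = 0.41 points per day.
- Uniform enrolment: one third of infants enter after 48 h, with a mean overlap of 12 h. This averages 4 h, or 1/6 day, per infant. So q = 0.41/6 = 0.07 points, or 0.4 infants per arm of 550.
- All at 72 h: one full day, so q = 0.41 points, or 2.3 infants per arm.

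**Step 3: effect on power.** The planned risk ratio is 0.16/0.23 = 0.696 and applies only to events after randomisation.
- As written: control 0.23; treated q + (0.23 − q) × 0.696.
- After the fix: control 0.23 − q; treated (0.23 − q) × 0.696.

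| q (points) | Risks as written | RR as written | Power as written | Risks after fix | Power after fix |
|---|---|---|---|---|---|
| 0 | 23.0% v 16.0% | 0.696 | 81.5% | 23.0% v 16.0% | 81.5% |
| 0.07 | 23.0% v 16.0% | 0.697 | 81.3% | 22.9% v 16.0% | 81.4% |
| 0.41 | 23.0% v 16.1% | 0.701 | 80.0% | 22.6% v 15.7% | 80.6% |
| 0.5 | 23.0% v 16.2% | 0.702 | 79.6% | 22.5% v 15.7% | 80.4% |
| 1 | 23.0% v 16.3% | 0.709 | 77.7% | 22.0% v 15.3% | 79.3% |
| 2 | 23.0% v 16.6% | 0.722 | 73.4% | 21.0% v 14.6% | 76.9% |

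The last three rows show what a hazard concentrated at 48–72 h would do. Two points is 11 infants per arm. It needs a hazard in that day of about 29 times the average under uniform enrolment (2/0.068), or about 5 times if everyone enrols at 72 h (2/0.41).

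The absolute risk difference is the same with and without the fix, because the removed events sit equally in both arms. The gain comes from a lower event risk, hence a smaller variance, and from a risk ratio restored to 0.696.

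**The case against.** The strongest reply is that the article never says outright that a culture taken before entry counts. The aim and background classify sepsis by age, and the outcome is a headline definition. How a pre-entry culture is recorded could be settled in the case report form, full protocol or analysis plan, none of which is shown. That stands in part: it cannot be claimed that such events were in fact counted. But the article itself fixes both times, and someone following its text would count them.

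A reader might also infer a substantial loss of power. The documents do not support that. Only infants enrolled after 48 h are exposed, for at most 24 h of a window that runs to term or discharge, and nothing in the article points to a concentration of sepsis in that day. Nor is the whole loss recoverable, since the fix itself removes events: at 1 point, power is 77.7% as written and 79.3% after the fix, against 81.5% with no such events.

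A reader might further infer bias or a false-positive risk. That does not follow either. Events before randomisation are balanced in expectation, so neither arm is favoured and the type I error is unaffected.

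**Conclusion.** The overlap is in the text, and anchoring the outcome at randomisation is the better rule. The effect is a slight dilution towards a risk ratio of 1. Under an even hazard, power at 550 per group goes from 81.5% to between about 81.3% and 80.0%, and the fix brings it to between about 81.4% and 80.6%.

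This rests on the 56-day even hazard and the two enrolment patterns, neither of which is in the documents. A higher sepsis rate on the third day of life, or randomisation later than enrolment, would raise the share. Early enrolment, or the longer window of infants born well before 32 weeks, would lower it. The point is worth acting on because it concerns the primary endpoint and costs little. It is not a flaw that threatens the trial.

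**What to change.** In the Aim and Outcomes sections, count as primary events only definite sepsis episodes whose positive culture was taken after the later of 48 hours of age and randomisation, up to the existing end of the window. The anchor should be randomisation, not first dose, which comes after allocation. Keep every randomised infant in the denominator, so intention to treat is preserved. Report positive cultures before randomisation as a baseline characteristic.

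An infant with such a culture would count only if a new episode follows. That needs a pre-specified rule, set blind to allocation, for telling a new episode from persistence of the first. With more than 900 infants already enrolled (Discussion), the rule can still be fixed before the final analysis, provided culture and randomisation times have been recorded.

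The costs are a sentence in the definition, the new-episode rule, slightly fewer events, and a small departure from the 48-hour definition under which the 23% planning rate is presented.

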## Methods/Design

### Trial Design

#### • Type of trial

This is a multi-centre, prospective, randomised, double blind, placebo controlled trial investigating the treatment of very preterm infants with a probiotic combination comprising *Bifidobacterium infantis, Streptococcus thermophilus *and *Bifidobacterium lactis *("ABC Dophilus Probiotic Powder for Infants^®^", Solgar, USA). The study powder contains 1 × 10^9 ^total organisms per 1.5 gm.

#### • Subjects and centres

A total of 1,100 subjects are being recruited and randomised from 12 perinatal centres around Australia and New Zealand (The Royal Women's Hospital, The Mercy Hospital for Women and Monash Medical Centre in Victoria; Royal North Shore Hospital, The Royal Prince Alfred Hospital, The Royal Hospital for Women, Liverpool Women's Hospital, Westmead Hospital and John Hunter Hospital in New South Wales; The Royal Hobart Hospital in Tasmania; and Auckland City Hospital and Christchurch Women's Hospital in New Zealand). Victorian recruits are offered the opportunity to participate in allergy assessments at 12 months' corrected age via maternal telephone questionnaire or assessment at The Royal Children's Hospital, Melbourne.

Parents are approached to consent to their baby's participation in the trial if they satisfy the inclusion and exclusion criteria (see below). Parents are provided with their own copy of the Patient Information and Consent Form and written consent is obtained from them. Infants enrolled from the Victorian centres are offered the opportunity to participate in allergy assessments at 12 months' corrected age, with consent for this being sought during the primary hospital admission.

#### • Duration of participation

Infants are given the probiotic or placebo from soon after the start of milk feeds until discharge home or term corrected age, whichever comes first. Victorian infants are followed until 12 months' corrected age.

#### • Timeline

Start of trial: October 2007

Recruitment period: estimated to be completed by March 2012

Time frame for statistical analysis: 6 months

Time frame for manuscript preparation: 6 months

The duration of the study is expected to be about 5 years from the beginning of subject recruitment, until the last data collection point.

#### • Study population

##### Inclusion criteria

a. Preterm infants both below 1500 g and less than 32 weeks' gestational age at birth

b. Enrolled within 72 hours of birth

##### Exclusion criteria

a. Major or suspected major congenital anomalies

b. Considered likely to die within 72 hours of birth

c. Parents from whom informed consent cannot be obtained. Babies of mothers who are already taking supplemental probiotics by capsule (not yoghurt, etc.)

### Outcomes

• **The primary outcome is the incidence of at least one episode of definite (blood culture positive) late onset sepsis before 40 weeks corrected age or discharge home, whichever occurs sooner.**

• The secondary outcomes are:

- incidence of clinically-suspected sepsis (blood culture negative sepsis)

- NEC, graded by modified Bell's criteria [37]

- mortality

- duration of the primary hospital admission

- number of courses of antibiotics

- number of days until full enteral feeds established (120 ml/kg/day or more for 3 consecutive days)

- In a subgroup of Victorian subjects at 12 months' corrected age:

(i) growth, including weight, length and head circumference

(ii) infections, hospital admissions and antibiotic courses

(iii) cumulative incidence of allergic disease, including atopic eczema, food allergy, and asthma/wheeze at 12 months as assessed by questionnaire [69,70]

(iv) immunological parameters including serum immunoglobulins, number of T- regulatory cells (Tregs) and levels of T- regulatory cytokines (Interleukin-10 and Transforming Growth Factor-β (TGFβ)) produced by mononuclear cells in-vitro [70].

(v) allergic sensitisation at 12 months - skin prick testing to a panel of common allergens (Egg white, milk, peanut, cat hair, grass pollen and house dust mite)

### Intervention and quality control

#### • Product description/Composition

The probiotic is the "ABC Dophilus Probiotic Powder for Infants^®^", Solgar, USA, containing 1 × 10^9 ^of total organisms/daily 1.5 g dose in a maltodextrin powder. This consists of *Bifidobacterium lactis, Streptococcus thermophilus *and *Bifidobacterium infantis*. The placebo looks identical to the probiotic and consists of maltodextrin. The maltodextrin powder contains 4 kcal/gram and is dairy free, gluten free and suitable for vegans. The daily dose is 1.5 g of study powder, irrespective of infant's weight or postnatal age.

#### • Confirmation of quality and safety of the probiotic

"ABC Dophilus Probiotic Powder for Infants^®^" is imported from Solgar, USA. This research team holds the import license obtained from the Australian Therapeutic Goods Administration Clinical Trial Notification (CTN) Scheme. The Solgar Company certify the quality of product through their established company protocols and ensure the correct transport of product to the pharmacy at The Royal Women's Hospital, Melbourne.

Taxonomy and quality of the probiotic organisms was confirmed by [name] of The Alimentary Pharmabiotic Institute, Cork, Ireland. Each batch of study and placebo powder is tested for the presence of pathogens using standard microbiological techniques and for the presence and quantitation of the probiotic organisms using real-time polymerase chain reaction techniques. This testing is undertaken at the microbiology laboratories of The Royal Children's and Women's Hospitals, Melbourne.

#### • Packaging and labeling with blinding

The probiotic and placebo powders are identically packaged by The Royal Women's Hospital Pharmacy Department, which holds the randomisation code. Each jar of study powder is identified with this unique code as well as the infant's medical record number following randomisation.

#### • Product handling

All study powder is supplied by Solgar^®^, USA. It is distributed by The Royal Women's Hospital Pharmacy Department to the individual study sites, where it is stored in a refrigerated dry environment at 4°C temperature. The investigators agree not to supply the study powder to any person except the infants participating in this trial.

### Management of subjects

#### • Route of administration

The study intervention/placebo is given orally or via gastric tube once daily, unless the feed volume is less than 3 mL when one level ProPrems trial measuring spoon of powder is administered in 1.5 mL feed twice daily. Freshly expressed mother's breast milk is the feed of choice followed by frozen breast milk, if fresh is not available. Banked breast milk is used when mother's milk is not available in centres with established protocols that use breast milk banking. Formula is used only when there is insufficient breast milk or if the mother chooses not to provide breast milk. Tube feeding is commenced as soon as possible in small and increasing amounts according to local protocols and the discretion of the treating neonatologist. Intravenous fluids and nutrition are used until approximately 120 ml/kg of milk is tolerated per 24 hour period. Feeding protocols aim to maximise the use of enteral feeding and minimise the use of central venous lines.

#### • Confirmation of probiotic colonisation

In Victoria, infants' stool carriage of probiotic species is documented to test for colonisation prior to the first dose of probiotic or placebo and then at 1, 4, and 8 weeks from treatment, and at 6 and 12 months' corrected age. Stool swabs are rotated in 200 μL of phosphate buffered saline (PBS) and DNA extracted as per the methods described by Furet, et al and Matsuki, et al. [71,72]. Extracted DNA is tested by quantitative real-time PCR for *Bifidobacterium infantis*, *Bifidobacterium lactis *and *Streptococcus thermophilus *using primers and probes directed at a 16S rRNA and 16S-23S integrated spacer gene respectively [73,74]. These methods are more sensitive than conventional culture techniques with detection limits of approximately 1 colony-forming unit/ml. This testing is undertaken at the Women's Centre for Infectious Diseases Molecular Microbiology Laboratory, The Royal Women's Hospital, Melbourne.

#### • Compliance

The probiotic study powder is administered, as ordered on the medication chart, until the baby reaches term corrected age or is discharged home from hospital, whichever comes first. Administration is monitored by the research team at each study centre.

#### • Allergy assessment at 12 months' corrected age

Infants enrolled at the 3 Victorian sites are eligible for the 12 month corrected age allergy assessment. This is coordinated by a study nurse and involves either a maternal telephone questionnaire or an assessment at The Royal Children's Hospital (RCH), Melbourne. Parents who consent to their infants' being assessed at 12 months' corrected age are asked to keep a written record of any infections, hospital admissions or allergic symptoms experienced by their child during this time period.

There are several components to the allergy assessment:

(i) A parental questionnaire is used to assess the incidence and severity of atopic eczema, food allergies and wheeze from term until 12 months' corrected age. This is a validated questionnaire which has been adapted from the Probiotic Eczema Prevention Study (Principal Investigator [name]) [70].

(ii) Where permission is given on the day, a blood sample (1 - 2 ml) is collected following the application of a topical anaesthetic (Emla 5%) to minimize distress to the child. Serum and peripheral blood mononuclear cells are isolated for future batched analysis of serum immunoglobulins, number of Treg cells, and in-vitro production of IL-10 and TGFβ levels. These studies will be performed at the Murdoch Children's Research Institute ([name], Allergy and Immune Disorders Research Group).

(iii) Skin-prick testing (SPT) is offered to determine sensitization to common allergens (Egg white, milk, peanut, cat hair, pollen, house dust mite (DerP1), 10 mg Histamine and a negative control). Participants with SPT responses ≥3 mm above the negative control are referred to the Paediatric Allergy Service for further assessment and management, including confirmatory oral food challenge if required.

#### • Study withdrawal

In the case of early withdrawal from the study, a research nurse records any reason given for withdrawal and attempts to collect as much data as possible on the Case Report Form. If Victorian parents refuse to continue the study treatment, they are asked if they are willing to participate in the 12 month follow-up questionnaires. If parents do not agree, they are not contacted any more. If participant withdrawal amounts to > 1% ie.11 subjects, 1% additional subjects will be recruited to compensate for missing data. Minimal data is collected on infants whose parents decline to be involved in the study, to ensure that participants are representative of the eligible population to ensure that the denominator can be estimated.

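### Victorian parents who stop the study powder are offered only the 12-month questionnaires, so missing growth, skin-prick and immunology data can depend on stopping treatment

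*Protocol article*

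**What the plan says.** Two rules stand together in the Study withdrawal section of the protocol article.

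- The first covers early withdrawal at any centre. A research nurse records any reason given and "attempts to collect as much data as possible on the Case Report Form".
- The second covers parents in Victoria who no longer want the powder: "If Victorian parents refuse to continue the study treatment, they are asked if they are willing to participate in the 12 month follow-up questionnaires". It continues: "If parents do not agree, they are not contacted any more".

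The section on the 12-month allergy assessment describes what Victorian families are offered in general. The assessment "involves either a maternal telephone questionnaire or an assessment at The Royal Children's Hospital (RCH), Melbourne". A blood sample is taken if permission is given on the day, and skin-prick testing is offered.

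The Outcomes section lists five 12-month outcomes for the Victorian subgroup: (i) growth, (ii) infections, admissions and antibiotic courses, (iii) allergic disease by questionnaire, (iv) immunological measures and (v) skin-prick sensitisation.

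On the analysis population, the Statistical Analysis section says "Data from all randomised participants will be considered in the intention-to-treat model (for the primary outcome"). It makes no matching statement for secondary outcomes.

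**The concern.** Refusing more powder and leaving the study are different events. A family can decline treatment and still be content for the child to be measured and tested. The article puts both under one heading and, for Victorian families who decline powder, names only the questionnaires. If staff follow that wording, the hospital visit is no longer put to them.

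Stopping powder happens after randomisation. If the offer of a measurement depends on it, the infants measured at 12 months are a subset selected partly by how treatment went. Randomisation does not guarantee that such subsets are comparable. Bias follows if stopping is related to the later outcome and its pattern differs between arms. The article gives no reasons for stopping, so this is a possibility and not an established fact. It still matters, because the effect of probiotics on allergic disease is the article's stated secondary aim, and sensitisation and immune measures are part of the evidence for it.

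**Working it through.** The article's only figures near this point concern the primary outcome, so I checked those first and then set the passages side by side.

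**1. The sample size, to see where the harm could fall.** Inputs from the sample size section: 23% v 16%, two-sided 0.05, power 0.80, 530 per group.

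- Mean proportion: (0.23 + 0.16)/2 = 0.195.
- Uncorrected n = [1.960 × √(2 × 0.195 × 0.805) + 0.842 × √(0.23 × 0.77 + 0.16 × 0.84)]² / 0.07² = (1.098 + 0.470)² / 0.0049 ≈ 502.
- With continuity correction: (502/4) × [1 + √(1 + 4/(502 × 0.07))]² ≈ 530.

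The stated 530 is reproduced. Recruiting 1,100 leaves 1,100 − 2 × 530 = 40 infants to spare, or 40/1,100 = 3.6%. That margin belongs to the primary outcome. It says nothing about the Victorian 12-month outcomes, for which the article gives no sample size.

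**2. What each Victorian family is offered at 12 months, as written.**

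| Outcome | Needs | Family continuing powder | Family refusing powder |
|---|---|---|---|
| (i) growth | measurement in person (my inference) | available through the hospital option | not named in the offer |
| (ii) infections, admissions, antibiotics | parental report | yes | yes, if parents agree |
| (iii) allergic disease | questionnaire | yes | yes, if parents agree |
| (iv) immunology | blood sample | optional, at the visit | not named in the offer |
| (v) sensitisation | skin-prick test | optional, at the visit | not named in the offer |

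The article does not say how growth is obtained. A telephone questionnaire cannot measure weight, length or head circumference, so I take it that a visit is needed. If growth comes from another source, it drops out of the point and (iv) and (v) remain.

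**3. How large the loss could be.** In one arm of the Victorian subgroup, let s be the proportion who stop powder, v the uptake of the visit among those who continue, and w the uptake among those who stop, had they been offered it.

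- Observed for visit-based outcomes under the written rule: (1 − s)v.
- Observed if everyone has the same choice: (1 − s)v + s·w.
- Loss due to the rule: s·w, which cannot exceed s.

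The article gives none of s, v or w, so no number can be put on this. The formula does show that the loss is partial: even with the offer restored, only a share w of those who stop would attend.

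**4. Whether other text protects these outcomes.** The intention-to-treat statement is confined to the primary outcome. The same withdrawal section provides for recruiting 1% more infants if withdrawals exceed 1% (11 infants). Extra recruits restore numbers but do not make the measured infants representative of those randomised.

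**The case against.** The strongest reply is that the sentence makes an offer and does not exclude anyone. Eligibility for the 12-month assessment is set by enrolment at a Victorian site, with no condition that treatment continues, and consent for it is sought during the primary admission. On that reading the questionnaire request is a minimum and the visit stays open. Since blood and skin-prick tests are optional for all and a telephone questionnaire suffices for any family, these data will be incomplete among continuing infants as well.

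Much of this stands, and it limits the effect. It does not remove the point. The article itself treats the questionnaire as the alternative to the hospital visit, so naming only the questionnaires is a narrower offer, and parents who decline them are not approached again. An optional test that is offered differs from one that is no longer offered because treatment stopped. Nor is this a detail lost in condensing the protocol: the article states a specific rule, and the criticism is of that rule.

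A reader might infer three stronger things that the documents do not support.

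- **That in-hospital outcomes go missing when powder stops.** Nothing says that recording ends then. The nurse is told to gather what data can be gathered, the Data management section promises every effort on follow-up, and the primary analysis takes all randomised infants. What remains is an ambiguity: the no-contact sentence does not say whether recording from the hospital chart continues.
- **That infants outside Victoria lose planned data.** The allergy follow-up is Victorian by design: "Victorian infants are followed until 12 months' corrected age". Infants elsewhere have no 12-month assessment to lose.
- **That a number of lost sepsis events can be calculated.** This would need an assumed stopping rate, complete loss confined to one arm of a blinded trial, the 31% risk quoted for infants under 1000 g applied to everyone who stops, and events removed while the infants stay in the denominator. The article supports none of these.

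**Conclusion.** The point holds for the Victorian 12-month secondary outcomes that need a visit: skin-prick sensitisation, immunology and, on the inference above, growth. As written, the offer of these measurements narrows when parents refuse further powder, so whether they are missing can depend on a post-randomisation event, and no stated analysis commitment covers them. The effect is partial and its size cannot be stated from the article. Whether it biases the comparison depends on why families stop and whether that differs by arm, which the article does not report. It does not show a threat to the primary outcome or its power. The change is worth making because it is cheap and removes an avoidable source of selection from a stated secondary aim.

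**What to change.** In the Study withdrawal section:

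1. Define two separate events: stopping study powder, and withdrawing consent for data collection. Only the second ends follow-up.
2. For Victorian families who stop powder, replace the questionnaire-only request with the choice already described in the 12-month allergy assessment section, namely the questionnaire or the hospital assessment, with blood and skin-prick testing optional as for everyone else.
3. For clarity, state that case report form recording from the hospital chart continues at all 12 centres to 40 weeks or discharge unless consent for data is withdrawn. The section already accepts limited recording for families outside the trial: "Minimal data is collected on infants whose parents decline to be involved in the study".

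The cost is a short amendment to the protocol and consent wording, a few extra visits in a clinic that already runs, and one more question to parents who have just declined treatment. That last item is a real, though small, burden on families.
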